### Variables

Before the intervention, a baseline patient survey will measure the following independent variables: participants’ demographic characteristics, socioeconomic derailers to pursuit of transplant, medical mistrust, health-related quality of life (HRQOL), health literacy, and the amount of previous transplant education they have received. It will also assess the following dependent variables: level of current transplant knowledge, current ability to make an informed decision about transplant, self-efficacy to pursue DDKT and LDKT, and steps taken toward transplant. After the intervention, a post-survey will measure key study dependent variables to assess change, including the level of current transplant knowledge, current ability to make an informed decision about transplant, self-efficacy to pursue DDKT and LDKT, and steps taken toward transplant. For patients randomized to receive the *ET@Home* education, it will also assess their experiences with the educational materials through a program evaluation assessment.

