#### Outcome measures and research methodology

In order to verify and demonstrate impact on improving knowledge of the process, risks, advantages, and disadvantages of deceased and living donation among dialysis patients, an RCT will be conducted. In this RCT, 1200 CKD patients in the KPSC system will be randomized to one of two education conditions (patient-guided *ET@Home* vs. standard KPSC transplant education, 600 patients per condition). Changes in key outcomes will be assessed comparing patient data collected at baseline and six months post-baseline. The primary outcome measures include patients’ knowledge of CKD and the risks and benefits of transplant and the capacity to make an informed decision about transplant. Additionally, key secondary measures will be examined, including self-efficacy to pursue DDKT and LDKT and steps taken towards transplant.

Comparisons in the two educational conditions’ effectiveness will also occur for patients earlier in the CKD continuum, patients who speak Spanish, and non-White patients.

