### Evaluation and statistical analysis plan

#### Power analysis

Based on the following assumptions, we estimated the sample size for the RCT. Using data from previous RCTs [4, 35], a mean knowledge change score of 1.0 points is estimated necessary to be detected among patients receiving *ET@Home* and standard KPSC education. Patients’ baseline transplant knowledge scores will be correlated with those of other patients from the same clinics [intraclass correlation coefficient (ICC) of 0.31]. The variance in knowledge change has both between- and within-cluster components, yielding a pooled standard deviation estimate of 4.0. Participant retention will be 50% at the 6-month assessment. Outcomes will be assessed using two-tailed statistical tests. Type 1 error rate (alpha level) will be set at 0.05. This study design will ensure power of 0.90. Power calculations for this trial are based on all of these factors, which yields a standardized effect size, accounting for clustering of approximately 0.257.

Power analyses based on changes in transplant knowledge, our primary study outcome, are presented. The study design and analyses were treated as a test of the difference between the mean knowledge score change of CKD patients in the *ET@Home* and standard KPSC education (control) conditions six months post-baseline. It is estimated that with 600 completed surveys (50% attrition), there will be a 90% power to detect a 0.25 effect size between two equal-sized groups (control and treatment groups). By stratifying recruitment and randomization by race/ethnicity (Asian, Black, Hispanic, White), primary language spoken (English vs. Spanish), and stage of CKD, according to the table below, this sample size will also have 90% power to detect 1 point differences in change on the transplant knowledge scale between the *ET@Home* and standard KPSC education conditions for these critical subgroups using interaction terms (e.g., treatment by race interaction, language by race interaction). Patients enrolled and randomized are shown in Table 3.

**Table 3 Tab3:** Patients enrolled and randomized

Race/Ethnicity/Language	Stage of CKD			
	3^a^	4	5/ESRD	Total
*English-speaking Asian*	67	67	66	200
*English-speaking Black*	67	66	67	200
*English-speaking White*	67	67	67	200
*English-speaking Hispanic*	67	67	66	200
*Spanish-speaking Hispanic*	133	133	134	400
Total	400	400	400	1200

^a^
*CKD* 3 patient recruitment prioritized based on likelihood to progress

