### Statistical analysis

The available demographic and clinical characteristics of patients who refuse to join the study will be compared to those who enroll to determine if the patient selection procedure has resulted in a biased sample. A similar analysis will be conducted to compare the patients who fail to complete the six-month assessment. Multiple imputation by chained equations (MICE) will be used to multiply impute missing data. Imputation models will include all analysis and stratification variables. The intent-to-treat (ITT) approach will be applied in that all study participants will be analyzed according to the group that they were randomized to, regardless of whether they actually received their assigned intervention or not. Responses to the six-month intervention evaluation will be summarized for the sample overall and by levels of the stratification factors.

It is hypothesized that patients earlier in the CKD continuum, patients who speak Spanish, and non-White patients will have less knowledge about the opportunities for and risks and benefits of living kidney donation and will be making less-informed LDKT decisions. Investigators will evaluate these hypotheses using data from the pre-survey (baseline) by fitting multilevel random effects models with a random intercept to account for clustering at the CKD clinic level to compare differences in knowledge, informed decision-making, and Self-Efficacy. First, unadjusted models will be examined with the race/ethnicity, primary language spoken, and stage of CKD as independent variables for each test (separate models for each). Then, each of these models will be adjusted for other factors hypothesized to impact each outcome, including level of socioeconomic vulnerability, the level of previous transplant education received, the level of medical mistrust, and the level of health literacy. The addition of these variables will help test and control for confounding.

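### With half of the six-month outcomes expected missing, the stated imputation model does not take in dropout predictors or some baseline measures already collected; adding them is a free improvement of modest, conditional value

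*Protocol article*

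**What the plan says.** The Power analysis section of the Protocol article states: "Participant retention will be 50% at the 6-month assessment". With "patient-guided *ET@Home* vs. standard KPSC transplant education, 600 patients per condition", about 600 of the 1200 patients would have no six-month survey.

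The Statistical analysis section handles this with multiple imputation by chained equations and describes the models in one sentence: "Imputation models will include all analysis and stratification variables". Just before it, the section compares refusers with enrollees on available demographic and clinical characteristics, and adds: "A similar analysis will be conducted to compare the patients who fail to complete the six-month assessment". No sentence says what follows for the imputation if that comparison finds differences.

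The variables named in the analyses are:
- **Aim 1 (baseline).** Knowledge, informed decision-making and self-efficacy are the outcomes, with a random intercept for clinic. Race/ethnicity, language and CKD stage are the predictors. The adjusted models add socioeconomic vulnerability, previous transplant education, medical mistrust and health literacy.
- **Aim 2 (trial).** The models hold change in knowledge and self-efficacy from baseline, informed decision-making, the count of new steps, arm, clinic, and any baseline characteristic found out of balance. Interactions of arm with the stratification factors follow.

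The Variables section lists among the baseline survey measures "medical mistrust, health-related quality of life (HRQOL), health literacy, and the amount of previous transplant education they have received". Age and gender come from the medical record (Demographic and clinical characteristics). Quality of life, age and gender are in no named outcome model.

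**The concern.** Multiple imputation can correct for dropout only through variables that are in the imputation model. With half of the primary outcomes imputed, the choice of those variables matters more than usual. The plan will look for characteristics that distinguish non-completers but does not commit to using them. The only stated route by which a further baseline variable enters the Aim 2 models is imbalance between arms, and that is a different property: a variable can be balanced at randomization and still predict who answers at six months.

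Two things are at stake. One is precision, if an unused baseline variable predicts the outcome beyond those already included. The other is bias in the arm difference, if such a variable also relates to dropout differently in the two arms. Differential dropout is conceivable here. The trial is unblinded, and only the ET@Home arm receives the mailed modules, postcards and optional text messages, so age or health status could affect retention in that arm more than in controls. The documents give no figure for this.

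**Working it through.** **Inputs from the Protocol article (Power analysis).** 1200 randomized 1:1; 50% retention; target "a mean knowledge change score of 1.0 points is estimated necessary to be detected"; SD of change from "yielding a pooled standard deviation estimate of 4.0"; two-sided alpha 0.05; and "It is estimated that with 600 completed surveys (50% attrition), there will be a 90% power to detect a 0.25 effect size".

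**Assumed inputs (no document figure).** r is the partial correlation of an omitted baseline variable with the change score, given what is already in the imputation model; I take 0.1 to 0.3. g is the log-odds of responding per SD of that variable; I take 0.5.

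**1. The plan's own figures.** 1200 × 0.50 = 600 completers, 300 per arm, so the expected extent of missing data reproduces. Power at 300 per arm and standardized effect 0.25 is Φ(0.25 × √(300/2) − 1.96) = Φ(3.062 − 1.960) = 0.865, against the stated 0.90. At the effect of 0.257 that the section also gives, it is 0.8825. That gap is a separate matter; 0.865 serves here only as the starting point.

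**2. What is already in the model.**

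| Variable | Plan-wide reading | Aim-2-only reading |
|---|---|---|
| Arm, clinic, race/ethnicity, language, CKD stage | in | in |
| Baseline knowledge and self-efficacy (part of the change scores) | in | in |
| Derailers (socioeconomic vulnerability), mistrust, health literacy, previous education | in (Aim 1 covariates) | out unless imbalanced |
| Quality of life, age, gender | out unless imbalanced | out unless imbalanced |
| Other predictors of dropout found by the completer comparison | not linked | not linked |

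**3. Precision.** With half of the outcomes missing, adding the variable multiplies the variance of the arm difference by 1 − 0.5r². Effective completers are 600 divided by that factor.

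| r | Variance factor | Effective completers | Power at 0.25 |
|---|---|---|---|
| 0 | 1.000 | 600 | 0.865 |
| 0.1 | 0.995 | 603 | 0.866 |
| 0.2 | 0.980 | 612 | 0.871 |
| 0.3 | 0.955 | 628 | 0.880 |

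**4. Bias in the arm difference.** Take the omitted variable A as standard normal and the probability of responding as 1/(1 + exp(−gA)), which averages 50%. The mean of A among responders is m(g) = E[A/(1 + exp(−gA))]/0.5. Numerical integration gives m(0.5) = 0.236. Omitting A shifts an arm's mean change by 4.0 × r × m(g), and the arm difference is biased by the difference between the two shifts.

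| Dependence of response on A | r = 0.1 | r = 0.2 | r = 0.3 |
|---|---|---|---|
| Same in both arms (g = 0.5, 0.5) | 0 | 0 | 0 |
| One arm only (g = 0.5, 0) | 0.09 | 0.19 | 0.28 |
| Opposite directions (g = 0.5, −0.5) | 0.19 | 0.38 | 0.57 |

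Entries are in knowledge points, against a target of 1.0. For r = 0.3 in one arm: 4.0 × 0.3 × 0.236 = 0.28. A simulation of the same scenarios gave 0.10, 0.17 and 0.30 for the one-arm row, and a bias of about zero in every scenario once A was used. The full SD of 4.0 is used; the SD left after the included variables would be smaller, so these values lean high.

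**The case against.** The strongest case against is that the quoted sentence states the accepted minimum for multiple imputation and excludes nothing. That stands: there is no word such as only, so a reader who infers a closed list goes beyond the text.

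It is also tempting to say that imputation would rest on arm and strata alone and so add almost nothing to a completer analysis. The documents do not support this. The change scores bring in baseline knowledge and self-efficacy, and clinic is in every model. On a plan-wide reading, which the wording allows because the sentence precedes both aims and is tied to neither, the four Aim 1 covariates are in too. They drop out only if the sentence is read for Aim 2 alone, and the text does not settle which is meant.

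A reader might also take the bias from a simple completer contrast as the bias of the plan. With an omitted variable at correlation 0.3 and log-odds 0.7 in one arm, that contrast is about 1.38 instead of 1.0. But it ignores the predictors that the plan does include. With one included baseline predictor carrying part of the association (assumed correlation 0.3 to 0.5 with the omitted variable), imputation without the auxiliary gave 1.05 to 1.18.

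Finally, a condensed article may leave the list of auxiliary variables to a full analysis plan. That has force and is why this is not called an error. The article does, however, state the content of the imputation model, and a better content is available from data already collected.

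**Conclusion.** The point holds as a free improvement, not as a mistake in the plan. The stated imputation content leaves the completer/non-completer comparison without consequence, omits quality of life, age and gender unless they happen to be out of balance, and is ambiguous about the four Aim 1 covariates.

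The benefit is modest. Precision improves by 0.5% to 4.5% in variance for partial correlations of 0.1 to 0.3, which moves power at an effect of 0.25 from 0.865 to at most 0.880. Bias of about 0.1 to 0.3 points against the 1-point target requires both an omitted variable of that strength and a link to dropout in one arm only (log-odds 0.5 per SD). Opposite links in the two arms would double it, and equal links would give none. All of these inputs are assumptions. The documents show neither that such a variable exists nor that dropout will differ by arm, so they do not support a claim that the planned analysis is biased.

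**What to change.** Replace the imputation sentence in the Statistical analysis section with: *Imputation models will include all analysis and stratification variables for both aims and, as auxiliary variables, the remaining baseline measures (including HRQOL, age and gender) and any characteristic found to differ between six-month completers and non-completers, with imputation done separately by arm.*

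Naming both aims removes the ambiguity over the Aim 1 covariates. Imputing by arm lets the relation of each auxiliary to the outcome differ between arms. The cost is one sentence and a somewhat larger imputation model. Every variable is already collected, so there are no added patients, visits or survey items. The change should be fixed before six-month outcomes are seen.

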## Abstract

**Background:**

Five-year survival on dialysis is only 40%, compared to 74% with a deceased donor kidney transplant (DDKT) and 87% with a living donor kidney transplant (LDKT). An American Society of Transplantation (AST) Consensus Conference recommended that patients with chronic kidney disease (CKD) Stages 3–5 have the opportunity to learn about and decide which treatment option is right for them, particularly about LDKT. However, early education about LDKT and DDKT outside of transplant centers is inconsistent and often poor, with patients in CKD 3 and 4 and ethnic/racial minorities even less likely to receive it. A new randomized control trial (RCT), in partnership with Kaiser Permanente Southern California (KPSC), will assess knowledge gaps and the effectiveness of a supplementary video-guided, print and technology-based education intervention for English- and Spanish-speaking patients in CKD Stages 3, 4, and 5 to increase LDKT knowledge and decision-making. To date, no published LDKT educational interventions have studied such a large and diverse CKD population.

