## Background

There are 30 million Americans with chronic kidney disease (CKD) and at risk for kidney failure, and 660,000 patients with end-stage renal disease (ESRD). To sustain life, ESRD patients, 31% of whom are Black, 15% Hispanic, and 5% Asian, must either receive daily or weekly dialysis treatments or have a kidney transplant. The five-year survival rate for patients on dialysis is only 40%, compared to 74% for patients who receive a deceased donor kidney transplant (DDKT) and 87% for patients who receive a living donor kidney transplant (LDKT) [1]. Over 95,000 individuals are awaiting a DDKT in the United States, with more being added daily (based on OPTN data as of 06/08/2018).

Patients who receive kidney transplants live 5–15 years longer than if they remained on dialysis and have a better health-related quality of life (HRQOL), including a greater likelihood of being in the workforce during their critical earning years [2]. While LDKT is the medically optimal and most cost-effective renal replacement therapy (RRT) for patients with ESRD, LDKT rates have declined by 17% from 2004 to 2014. In 2014, in the U.S., 17,106 patients received a transplant (5536 LDKTs) while 8021 patients died or became too ill to remain on the list; 70% who died were racial/ethnic minorities. Of the 2281 transplants performed in California in 2017, only 604 were from living donors (OPTN data as of 06/08/2018).

Providing comprehensive education to CKD patients about the benefits of LDKT as early as possible can increase the chances that they will learn about it, seek living donors, and ultimately receive an LDKT [3]. Many patients, particularly socioeconomically disadvantaged patients and patients of racial/ethnic minority groups [4], have not had sufficient DDKT and LDKT education before their kidneys failed. [5, 6] Generally, patients not considering LDKT lack knowledge about the benefits of living donation over remaining on dialysis [7], have concerns about involving and risking a living donor’s health [7], fear asking others to donate a kidney [8], or fear their own surgical pain and the possibility of the transplanted kidney failing [9].

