## Study design

The purpose of this study is to assess whether the *ET@Home* program can be integrated successfully across a large racially, ethnically, and geographically diverse patient catchment area and to assess its effectiveness to increase knowledge about the risks and benefits of LDKT and increase informed decision-making. The effectiveness of the *ET@Home* program will be evaluated in a randomized controlled trial (RCT) of 1200 Black, Hispanic, Asian, and White patients with stage 3, 4, or 5 CKD. Patients will be randomized to receive: (1) no additional education other than what is provided within KPSC (standard-of-care); or (2) a video-guided, four-part *ET@Home* program delivered by mail and supported through bimonthly postcards and texting over six months. The study has two aims.

### Aim 1

Before intervention, to assess differences in knowledge and decision-making about the opportunities for and risks and benefits of living kidney donation for 1200 CKD Stage 3–5 patients by race/ethnicity and primary language spoken.

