#### Hypothesis

*Patients earlier in the CKD continuum, patients who speak Spanish, and non-White patients will have less knowledge about the opportunities for and risks and benefits of living kidney donation and will be making less informed LDKT decisions.*

### Aim 2

To conduct a randomized controlled trial in English and Spanish of *ET@Home* for CKD Stage 3–5 patients to assess its effectiveness to increase LDKT knowledge and decision-making by race/ethnicity and primary language spoken as compared to the standard KPSC education.

#### Hypothesis 1

*At the conclusion of the trial, CKD patients who receive ET@Home will have greater transplant knowledge and be more likely to make an informed treatment decision than patients receiving KPSC education alone.*

#### Hypothesis 2

*ET@Home will be more or equally effective for patients earlier in the CKD continuum, patients who speak Spanish, and non-White patients than patients in these subgroups receiving KPSC education alone.*

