While patients at all phases of CKD and their family members and support persons are welcome to attend the transplant education course, it is primarily focused on individuals who have reached an advanced stage of CKD and/or ESRD and are contemplating renal replacement options, or who are new to dialysis and considering transplant as a renal replacement approach. Patients who wish to be evaluated for transplant eligibility and move forward with the process of pre-transplant assessment and listing are required to complete this course before beginning pre-transplant work-up. For this trial, routine transplant education practices will be continued without any content changes. Patients who are randomized to the control condition and who are or become potentially eligible for transplant will not receive any additional interventions within KPSC during the study period.

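### Aim 1's second-step models adjust for previous transplant education and call it confounding control, although the protocol describes it as a route by which the knowledge gap arises

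*Protocol article*

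**What the plan says.** The Aim 1 objective in the Study design section is "to assess differences in knowledge and decision-making about the opportunities for and risks and benefits of living kidney donation", before intervention. The hypothesis is directional: "Patients earlier in the CKD continuum, patients who speak Spanish, and non-White patients will have less knowledge", and these groups will also be making less informed decisions about living donor transplant. Neither statement is conditional on equal education.

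The Statistical analysis section sets two steps, both with a random intercept for clinic:

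- Step one: "First, unadjusted models will be examined with the race/ethnicity, primary language spoken, and stage of CKD as independent variables for each test", with a separate model for each factor.
- Step two: each model is adjusted for socioeconomic vulnerability, previous transplant education, medical mistrust and health literacy, described as factors expected to affect the outcome. The stated purpose is: "The addition of these variables will help test and control for confounding".

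The text does not say which step decides the hypothesis.

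**The concern.** A confounder of a group difference must be a cause of group membership or share a cause with it. A variable that group membership influences, and that in turn influences the outcome, is a mediator. Adjusting for a mediator removes part of the difference under study.

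The protocol treats previous transplant education as the first kind of variable in the analysis section and describes it as the second kind everywhere else. If patients know less because they were taught less, the education-adjusted gap will shrink. Under the stated label, that shrinkage would be read as confounding explained away. Under the protocol's own rationale, it would show that the disparity works through missing education, which is what the programme is meant to supply. The stated purpose would therefore misdirect the reading of one of the trial's two aims.

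**Working it through.** **1. The plan's own figure.** Aim 1 has no sample size, power or effect figure of its own, so there is nothing to reproduce. The core of the check is a comparison of texts.

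**2. Is previous education on the path?**

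- *Stage and race/ethnicity to education.* The abstract describes early education as inconsistent and often poor, with "patients in CKD 3 and 4 and ethnic/racial minorities even less likely to receive it".
- *Disadvantage and race/ethnicity to education.* The Background says that many patients, particularly disadvantaged and minority patients, "have not had sufficient DDKT and LDKT education before their kidneys failed".
- *Stage to education.* Of the standard KPSC course, the control description says "it is primarily focused on individuals who have reached an advanced stage of CKD and/or ESRD".
- *Language to education.* The same section has the course given monthly in English at 13 centers, with interpreters available, and in Spanish at only 1–2.
- *Education to knowledge.* The Discussion says that better transplant education can increase knowledge.

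Both links are therefore in the document. The reverse link is not plausible: earlier transplant education does not determine race, primary language or CKD stage.

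**3. Do the other three covariates share the problem?** The cited texts concern education received. They do not show that socioeconomic vulnerability, mistrust or health literacy results from CKD stage. For the stage contrast these may be ordinary confounders. The point is therefore confined to previous education.

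**4. What adjustment does to the estimate.** With total gap T and a share m of it running through education, a linear model gives:

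adjusted gap = T × (1 − m); unadjusted gap = T.

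A simulation with T = −1.0 point confirms this. The unadjusted estimate stayed between −0.98 and −1.02. The adjusted estimates were:

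| m | 0 | 25% | 50% | 75% | 100% |
|---|---|---|---|---|---|
| Adjusted gap | −0.98 | −0.74 | −0.49 | −0.25 | −0.01 |

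**5. Illustration of detectability.** All of these inputs are assumptions for Aim 1:

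- A gap of 1.0 point and an SD of 4.0, borrowed from the Power analysis section, where they describe change in knowledge during the trial and not baseline scores.
- Either SD 4.0 with clustering ignored, or a within-clinic SD of 4.0 × √(1 − 0.31) = 3.32, using the stated ICC.
- Group sizes from Table 3: stage 3 vs 5, 400 vs 400; Spanish vs English, 400 vs 800; non-White vs White, 1000 vs 200 (200 Asian + 200 Black + 200 + 400 Hispanic = 1000).
- The same standard error with and without adjustment, for simplicity.

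SE = SD × √(1/n₁ + 1/n₂); power = Φ(δ/SE − 1.96) + Φ(−δ/SE − 1.96), with δ = 1.0 × (1 − m).

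For non-White vs White, √(1/1000 + 1/200) = 0.0775, so SE = 0.310 (SD 4.0) or 0.257 (SD 3.32). With δ = 1.0 and SE = 0.310, Φ(3.23 − 1.96) = Φ(1.27) ≈ 0.90.

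The table gives the chance of a significant result, for SD 4.0 / SD 3.32:

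| Contrast | Unadjusted | m = 25% | m = 50% | m = 75% |
|---|---|---|---|---|
| Stage 3 vs 5 | 94% / 99% | 76% / 89% | 42% / 57% | 14% / 19% |
| Spanish vs English | 98% / >99% | 86% / 96% | 53% / 69% | 18% / 23% |
| Non-White vs White | 90% / 97% | 68% / 83% | 37% / 49% | 13% / 16% |

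At m = 100% the adjusted model rejects at the 5% error rate. These figures show the mechanism; they do not forecast this trial.

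**The case against.** The strongest reply is that the right test is already planned. The unadjusted models come first, address the total gap directly and keep their full power. Fitting unadjusted and then adjusted models is a common sequence in disparities research, and comparing the two can be informative. Which of two planned models takes precedence is a matter often left to a statistical analysis plan, and none is shown here.

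Most of this stands. A reader might infer that the adjusted models are the final or only test of Aim 1, or that the plan will reverse the Aim 1 conclusion. The text supports neither: it says only that adjustment follows, and nothing says that a significant unadjusted result will be set aside. A reader might also infer that all four covariates are mediators, which the documents do not show.

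What the reply does not remove is the stated purpose. The protocol fixes the covariate list and the reason for it, and for previous education the reason contradicts its own rationale. If the two steps disagree, the wording gives the appearance of validity to the step that does not test the hypothesis. A later analysis plan that follows the sentence would carry this forward.

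**Conclusion.** The point holds in a limited form. The Aim 1 sequence contains a direct test of the hypothesis, but the adjusted step is described as confounding control although it includes at least one variable that the protocol itself presents as a pathway. The education-adjusted coefficient answers a different question, and a smaller or null value would not count against the hypothesis.

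The estimate shrinks in proportion to the mediated share: to about half if half the gap runs through education, and to about zero if all of it does. That share, the baseline gap and the baseline SD are not in the documents, so the power figures are illustrations only. The conclusion about the label depends on none of them.

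The consequence is confined to the interpretation of Aim 1. Randomisation and the Aim 2 comparison of the two education conditions are unaffected.

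**What to change.** In the Statistical analysis section:

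1. State that the Aim 1 hypotheses are judged on models that do not include previous transplant education, namely the unadjusted models already planned. Allow a sensitivity model with any covariate justified as a true confounder of a particular contrast, for example socioeconomic vulnerability for CKD stage.
2. Replace the sentence on confounding with wording such as: models that include previous transplant education are explanatory; they estimate the difference that remains at equal prior education, and attenuation is read as a pathway for the disparity, not as evidence against it.
3. If power for Aim 1 is illustrated, say that the mediated share, baseline gap and SD are assumed, and use 1000 vs 200 for non-White versus White.

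The cost is a few sentences. No data, patients or new primary models are needed. The one thing given up is the right to cite the education-adjusted estimate as a confounder-controlled test of the hypothesis.
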